**Fig. 1 Fig1:**
[figure not shown]
Flowchart of the RESET-psychotherapy study

#### Randomization and blinding

Upon completion of the baseline assessment, patients are randomized by the coordinating researcher of the participating center (Fig. 1). Permuted block randomization is used, stratified per participating site, using Castor EDC software. Patients are randomly assigned to the control condition (TAU) or the experimental condition (TAU + TFT) on a 1:1 basis. Due to the nature of the TFT, patients and therapists are aware of the allocated arm. However, outcome assessors are kept blind to the allocation, in accordance to the CONSORT guidelines [58]. Unblinding of the outcome assessors is not permissible and the outcome assessors are instructed to remind participants to not disclose the nature of their treatment.

### Interventions

Participants in both treatment conditions are patients in specialized mental health care institutions, the Dutch equivalent of outpatient mental health care for patients with more complex and severe mental disorders.

#### Treatment as usual (TAU)

TAU for MDD is determined by the Dutch multidisciplinary practice guideline for depression [59]. This means that patients with MDD and CT receive good clinical care, e.g. evidence-based pharmacotherapy (antidepressant medication), combined with/or evidence-based psychotherapeutic interventions, such as CBT or interpersonal therapy (IPT). To determine the content of treatment, detailed information about the type of TAU, the number of sessions, treatment duration, treatment setting and treatment form is assessed by using a self-composed questionnaire that therapists need to complete after the post-treatment assessment (T2 at 12 weeks, see Table 1). Up to T2, TAU therapists are instructed to not provide TFT for CT to minimize treatment contamination [60]. To somewhat even the number of contact moments between the two conditions, patients in the control condition are offered extra contact moments with a RA when they complete the IDS questionnaire from home in week 2,4,8 and 10 (Table 1). In addition, patients in the control condition are encouraged to participate in monthly online group sessions in which a specific theme relevant to mental health (i.e. sleep, activity, stress) is discussed by an expert in this field. Because of these extra contact moments, the treatment for patients in the control group could be described as an enriched TAU.

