### Study procedures

#### Informed consent and baseline assessment

The RESET-psychotherapy study was approved by the Medical Research Ethical Committee (MREC) of the Amsterdam UMC location VUmc. Participants must personally sign and date the informed consent (IC) form before any study-specific procedures are performed. The IC procedure is executed by authorized RA’s. Written and verbal versions of the patient information letter and IC is presented to the participants, detailing the exact nature of the study, the implications and constraints of the protocol and any risks involved in taking part. After the participant has signed the IC, the two-hour baseline measurement is conducted by a RA (Fig. 1). During this assessment, a wide range of data is collected, see Table 1. The biological samples are only collected if the participant explicitly gives consent in the IC. Participants in the fMRI sub-study are asked to sign the IC of this sub-study during the first fMRI measurement before undergoing the fMRI scans (see ‘ Assessments, outcomes and instruments’ for the fMRI scanning protocol). The one-hour pre-treatment fMRI measurement must occur within 2 weeks after the baseline measurement (Fig. 1). If this is not possible, the patient cannot participate in the fMRI sub-study.

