#### Primary outcome

The primary outcome is self-reported depression symptom severity at post-treatment, measured with the 30-item IDS-SR [52]. This questionnaire measures the severity of depressive symptomatology during the previous seven days on a 4-point Likert scale, ranging from 0 to 3, with a higher total score indicating a higher severity of depressive symptoms. The IDS-SR has solid psychometrical properties with high internal consistency and good concurrent validity with the 17-item Hamilton Rating Scale for Depression [52].

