#### Secondary outcomes

##### Remission and depression symptom severity during treatment and at follow-up

To assess the trend of depression symptom severity during treatment and at 6-month follow-up, participants are asked to complete the IDS-SR online in weeks 2, 4, 8 and 10, at T1 and at T3. MDD remission is defined as a score of  ≤ 14 on the IDS-SR [65] and confirmed with the MINI-S [53]. Because of its brevity and good psychometric properties, this interview is especially convenient for diagnosing MDD patients in everyday clinical practice.

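### A control-only research-assistant contact coincides with completing the IDS-SR in weeks 2, 4, 8 and 10, so the during-treatment scores are collected under different conditions by arm

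*Protocol article*

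**What the plan says.** All places are in the protocol article.

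- **Treatment as usual (TAU).** The contact has a stated purpose, "To somewhat even the number of contact moments between the two conditions", and its form is that "patients in the control condition are offered extra contact moments with a RA when they complete the IDS questionnaire from home", in weeks 2, 4, 8 and 10. The section calls the result an enriched TAU.
- **Remission and depression symptom severity during treatment and at follow-up.** For the whole trial, "participants are asked to complete the IDS-SR online in weeks 2, 4, 8 and 10, at T1 and at T3". No RA contact is mentioned for the experimental arm in those weeks.
- **Background, objectives.** Secondary objective 1 compares the arms on depressive symptoms during treatment and at 6-month follow-up.
- **Primary outcome.** "The primary outcome is self-reported depression symptom severity at post-treatment, measured with the 30-item IDS-SR". The extra contact is not described for that occasion.
- **Randomization and blinding.** Patients and therapists know the arm. Outcome assessors do not, and "Unblinding of the outcome assessors is not permissible".
- **Informed consent and baseline assessment.** "the two-hour baseline measurement is conducted by a RA". Randomization follows that assessment.
- **Statistical analysis plan.** The linear mixed model has time-point indicators and a treatment-by-time term for each time point.

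**The concern.** Giving control patients some extra contact is a reasonable way to reduce an attention imbalance. The difficulty is the moment chosen. Contact with staff around a self-report form can change how items are answered and whether the form is completed at all. When this happens in one arm only, such an effect is fully confounded with treatment on those occasions. No later analysis can separate the two, because no control patient is measured under the experimental arm's conditions, or the reverse.

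The stake is the during-treatment comparison in secondary objective 1. A second, conditional stake is blinding. Because only control patients are offered the contact, the RA who makes it can tell the arm. Reminding participants not to disclose their treatment, the safeguard that the article describes, does not help against that. It would matter most for the MINI-S interview, which confirms remission; the IDS-SR is self-reported by patients who already know their arm.

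**Working it through.** **1. Occasions affected.** Post-baseline IDS-SR occasions are weeks 2, 4, 8 and 10, T1 (week 6), T2 (week 12) and T3: 4 + 3 = 7. The contact falls on 4 of the 7. Of the five occasions between baseline and T2 (weeks 2, 4, 6, 8, 10), it falls on 4.

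**2. The plan's own figure.** The article gives no number for the contact. Its sample size reproduces and is not altered by this point: 2 × (1.960 + 0.842)² / 0.50² = 62.8, so 63 per arm; 63 / 0.80 = 78.75, so 79 per arm and 158 in total.

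**3. Effect on the interim contrast (illustration).** Assumptions, none of them from the documents: the treatment effect builds up linearly to the design value of -0.50 SD at week 12, and the contact shifts every control score at weeks 2, 4, 8 and 10 by a constant *s* SD.

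- Mean week of the four occasions: (2 + 4 + 8 + 10) / 4 = 6.
- True mean interim contrast (experimental minus control): -0.50 × 6/12 = -0.25.
- Observed contrast: -0.25 - *s*.

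This was checked by simulation: 79 per arm, 300 runs per scenario, unit SD, correlation 0.85 between scores two weeks apart, and a likelihood fit with a separate mean for each arm at each visit. Drop-out was either none or 20% at random and equal in both arms.

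| *s* (SD) | Arithmetic | Simulated, no drop-out | Simulated, 20% drop-out | T2, no drop-out / 20% |
|---|---|---|---|---|
| 0 | -0.25 | -0.24 | -0.26 | -0.49 / -0.51 |
| -0.1 | -0.15 | -0.14 | -0.16 | -0.49 / -0.51 |
| -0.2 | -0.05 | -0.04 | -0.06 | -0.49 / -0.51 |
| -0.3 | +0.05 | +0.06 | +0.04 | -0.49 / -0.51 |

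The sign of *s* is unknown. With *s* = +0.1 to +0.3 the same arithmetic gives -0.35 to -0.55, so the interim benefit would be exaggerated instead.

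**4. Effect on T2.** The T2 contrast is the same at every shift. One run has a standard error of about √(2/79) = 0.159, so the mean of 300 runs has about 0.159/√300 = 0.009. Both -0.491 and -0.513 therefore agree with -0.50. The reason is structural: with a separate mean for each arm at each visit, a constant shift changes only the fitted means at the shifted visits. Residuals and covariances, and with them any borrowing for a missing T2 value, stay as they were.

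**5. Blinding.** The contact reveals the control arm to whoever makes it. The article attributes the baseline measurement to an RA, but that precedes randomization. Table 1 lists the MINI-S as an interview from T0 to T3 without saying who conducts it after baseline. As scheduled, two contacts (weeks 2 and 4) precede T1 and all four precede T2. So the route to unblinding exists if one person does both jobs, and the article does not state that anyone does.

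**The case against.** The strongest reply is that this is a deliberate and disclosed choice. The contact is part of the comparator, the article labels it enriched TAU, and the Discussion names a possible attention effect. Any genuine benefit from contact belongs to the control condition and is not measurement error. The contact is only offered, everyone completes the same form online, and the wording may mean around that occasion and not during completion. Nothing says that the RA administers the form or sees the answers. All of this stands, and it is why the size of any effect is unknown. It does not answer the coupling: attention can be balanced without attaching the contact to an outcome form, and neither the TAU section nor the Discussion addresses the timing.

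Two stronger readings are tempting, and the documents support neither.

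- **A breach of blinding.** A reader might infer that the plan contradicts its own rule on assessors. The article refers to several RAs, forbids unblinding, and never says that the contacting RA assesses the same patient. Who contacts whom is also a detail that an article may leave to the full protocol. What remains is a risk to guard against.
- **Bias in the primary result.** A reader might infer that the T2 estimate is distorted, or equate the 20% drop-out allowance with the share of T2 information borrowed from these scores. The contact is not described for T2, and the planned treatment-by-time terms absorb a constant interim shift. A missing T2 value is only partly recovered, and also from T0 and T1, so the drop-out fraction is not an information share.

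**Conclusion.** The point holds for the interim IDS-SR scores. By a rule that the plan states, four of seven post-baseline occasions are collected under arm-dependent conditions, and secondary objective 1 rests largely on them. Under the assumed linear build-up, a control-arm shift of 0.25 SD towards lower scores would cancel the mean interim contrast (-0.25 + 0.25 = 0), and a shift the other way would inflate it. Neither size nor direction is known, and since the article gives no SD for the IDS-SR, the shift cannot be put into scale points.

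The T2 primary contrast is not directly affected. That rests on the model keeping separate treatment-by-time terms, on a shift that is roughly constant across control patients, and on data missing at random. The blinding point is conditional on one RA both contacting and assessing the same patient. This is an inexpensive improvement to a secondary comparison and does not challenge the primary analysis.

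**What to change.** Keep the attention-balancing contact but separate it from measurement:

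1. Send identical online invitations and reminders for the week 2, 4, 8 and 10 IDS-SR in both arms.
2. Make the control-arm contact only after the form has been submitted, or on another day.
3. Do not let an RA who makes these contacts conduct that patient's T1, T2 or T3 assessment, and say so next to the blinding rule.

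The cost is minor scheduling work and some reallocation of existing RAs, with no extra visits or instruments. Recruitment was ongoing when the article was written, so a change of work instruction could apply to patients still to be enrolled. For scores already collected under the present rule, the difference in collection should be reported alongside the during-treatment results.

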#### Trauma-focused therapy (TFT)

In the experimental condition, patients receive 6 to 10, 60–90 min individual TFT sessions delivered over 12 weeks, in addition to TAU. Therapists that provide TFT do not provide TAU for the same patient. Depending on the life history of the patient, one or both of the following are the focus of TFT: 1) specific CT triggers of the current depressive episode (or earlier episodes); 2) belief systems that have originated from CT exposure. The type of TFT depends on the type of CT the patient reports in the CTQ-SF and during the case conceptualization: ImRs if the patient predominantly reports experiences of (physical and/or emotional) neglect and EMDR if the patient predominantly reports experiences of (physical, emotional and/or sexual) abuse [61, 62]. See Additional file 1: Appendix B for a more detailed description of the adjunctive TFT.

#### Therapists and training

TAU and TFT are performed by psychologists (or psychiatrists in case of medication), recruited from participating mental health organizations, who have at least a Master’s degree in Clinical Psychology and clinical experience in providing evidence-based depression treatments. In addition, most of the therapists have completed a comprehensive training in cognitive behavioral therapy. TFT therapists have to be qualified to provide both EMDR and ImRs. For EMDR, therapists must have at least completed a 4-day training. In addition, therapists are required to attend a 3-h study-specific EMDR training session which focusses on factors that need to be taken into account when providing EMDR for patients with MDD instead of PTSD (i.e. concentration problems and the amount of working memory taxation). For ImRs, therapists are obligated to follow a 2-day ImRs training consisting of didactic teaching and role-playing exercises. Therapists are instructed to strictly follow the EMDR and ImRs treatment protocol and attend monthly EMDR and ImRs supervision to monitor and uphold treatment fidelity. All TFT sessions are videotaped or audiotaped if the patient explicitly consents. A sample of randomly selected taped therapy sessions will be rated using the modified ImRs Therapist Adherence and Competence Scale [63] and a modified version of the EMDR treatment integrity checklist of De Roos and De Jong (2020) [64].

### Assessments, outcomes and instruments

After baseline, participants are re-assessed at three different time points over the course of nine months: 6 weeks after baseline (T1), 12 weeks after baseline (T2; post-treatment assessment) and 6 months after post-treatment (T3) (Fig. 1). A time window of 4 to 8 weeks after baseline is proposed for T1 and a time window of 10 to 14 weeks for T2. Participants receive a gift voucher of €25 for each completed assessment. Participants that take part in the fMRI sub-study will undergo the second, one-hour post-treatment fMRI assessment (identical to the pre-treatment assessment) as soon as the T2 assessment of the RESET-psychotherapy study has been completed (see Fig. 1). Participants of the fMRI sub-study receive a gift voucher of €15 for each completed fMRI assessment.

Table 1 presents an overview of all outcome measure instruments per time point.

#### Primary outcome

The primary outcome is self-reported depression symptom severity at post-treatment, measured with the 30-item IDS-SR [52]. This questionnaire measures the severity of depressive symptomatology during the previous seven days on a 4-point Likert scale, ranging from 0 to 3, with a higher total score indicating a higher severity of depressive symptoms. The IDS-SR has solid psychometrical properties with high internal consistency and good concurrent validity with the 17-item Hamilton Rating Scale for Depression [52].

#### Secondary outcomes

##### Remission and depression symptom severity during treatment and at follow-up

To assess the trend of depression symptom severity during treatment and at 6-month follow-up, participants are asked to complete the IDS-SR online in weeks 2, 4, 8 and 10, at T1 and at T3. MDD remission is defined as a score of  ≤ 14 on the IDS-SR [65] and confirmed with the MINI-S [53]. Because of its brevity and good psychometric properties, this interview is especially convenient for diagnosing MDD patients in everyday clinical practice.

##### Functioning and disability

To assess overall functioning and disability during the previous month, the 12-item WHO Disability Schedule (WHODAS) is administered. This instrument is internally consistent, reliable, and has an overall high correlation with other measures of disability [66].

##### Anxiety

The severity of anxiety symptoms is assessed with the 21-item Beck Anxiety Inventory (BAI), which contains items about physical and physiological symptoms and cognitive aspects of anxiety during the previous seven days [67]. Each item is rated on a 4-point scale with a higher total score indicating a higher severity of anxiety symptoms. The BAI has good psychometric properties, with good convergent and discriminant validity, internal consistency and test–retest reliability [67].

##### Insomnia

Insomnia complaints and consequences during the previous two weeks are assessed with the 7-item Insomnia Severity Index (ISI) [68]. Items are scored on a 5-point Likert scale, with higher scores indicating a higher insomnia severity. The ISI possesses adequate internal consistency, good face and content validity, and is sensitive to treatment response in clinical patients [69].

##### Subjective stress

The 14-item Perceived Stress Scale (PSS) is assessed to measure the degree to which individuals appraise situations as unpredictable, uncontrollable and overloading (general beliefs about stress) during the previous month [70]. Items are rated on a 5-point Likert scale, with higher scores reflecting greater perceived stress. The PSS contains two underlying factors (general distress and inability to cope), which are internally consistent and significantly correlated with depression scores, providing support for the predictive validity of the instrument [71].

##### Suicidality

Although not defined as a secondary outcome in the current study, a shortened version of the clinician-administered Columbia-Suicide Severity Rating Scale (C-SSRS) [72] is administered during the research assessments in case participants report repeated thoughts about death, suicide intentions or plans. The C-SSRS has good convergent and divergent validity with a significant sensitivity for change across suicidal ideation and behavior components [72].

#### Descriptive variables and clinical factors

At baseline, several demographic characteristics (e.g. age, sex and socioeconomic status) are collected using a general demographic questionnaire. In addition, information about Body Mass Index (BMI), current and/or past smoking and drug use is obtained. To screen for alcohol intake, dependence and adverse consequences, the 10-item Alcohol Use Disorders Identification Test (AUDIT) is administered [73]. The total score ranges from 0–40 with a cut-off score ≥ 8 indicating a potential alcohol problem. The AUDIT has proven to be a reliable and valid instrument [74]. To measure health-related physical activity, the 7-item self-report International Physical Activity Questionnaire (IPAQ) is used [75]. This short questionnaire asks about the level of physical activity in the last 7 days. At baseline, treatment characteristics of former and/or current depression treatments are assessed. Additional treatment characteristics are assessed by retrieving information (e.g. number of no-shows) from the electronic health record (EHR), and the content of TAU and TFT is assessed by using self-composed questionnaires that therapists complete after the post-treatment assessment (T2). During the 6-month follow-up assessment (T3), additional questions are asked concerning treatment history since the baseline measurement.

##### Comorbid PTSD or ASD

During the baseline assessment, the presence of a comorbid PTSD or ASD diagnosis is identified with the PTSD and ASD section of the MINI-S [53].

##### Timing, duration and context of CT

To obtain more detailed information about CT (age and context of CT exposure), and to examine whether these CT characteristics influence the effect of TFT, the 75-item Maltreatment and Abuse Chronology of Exposure questionnaire (MACE) is used [76]. This questionnaire assesses exposure to different CT types during each childhood year, providing an overall severity score and a multiplicity score. The MACE shows an excellent test–retest reliability and good convergent validity with the CTQ and the Adverse Childhood Experience (ACE) score [76].

##### Resilience

To obtain information about resilience, a measure of stress coping ability, the 2-item Connor-Davidson Resilience Scale (CD-RISC2) is used [77], an abbreviated version of the 25-item CD-RISC [78]. The scale is rated on a 5-point Likert scale (0–4), with a higher score reflecting greater resilience. The CD-RISC2 shows good test–retest reliability and validity and has proven to be a good representative of the overall scale [77].

##### Personality

To measure personality traits, the Neuroticism–Extraversion–Openness Five-Factor Inventory (NEO-FFI) is administered [79]. This 60-item questionnaire assesses the five domains of the Five-Factor Model (FFM; neuroticism, extraversion, openness to experience, conservativeness, agreeableness and conscientiousness), with items rated on a 5-point Likert scale (1 = strongly disagree to 5 = strongly agree). Each of the five domains of the NEO-FFI has been found to possess adequate internal consistency and temporal stability [79].

##### Coping

To measure coping style, the 16-item Coping Orientation to Problems Experienced Inventory (COPE) is assessed [80], a shortened version of the 28-item Brief COPE [81]. The COPE-16 contains 3 subscales: Problem Solving and Cognitive Restructuring Strategies, Avoidance Strategies, and Support Seeking Strategies. All three scales and associated items show acceptable reliability [80].

##### Stressful life events

Stressful life events are assessed with the List of Threatening Experiences (LTE) [82]. This brief self-report questionnaire comprises 12 questions with dichotomous responses (‘yes’/ ‘no’) about major stressful life events in the preceding 6 months. The LTE shows high test–retest reliability for the presence of any event over 6 or 3 months and good concurrent validity [82].

